### Metabolomics Analysis

Serum samples will be pre-processed, divided for the available targeted and non-targeted metabolomics methods, and dried. Samples will then be reconstituted and analyzed using metabolomic platforms. The preliminary targeted analysis will consist of mining for metabolites in the Krebs Cycle and others identified in previous studies (23–25). Secondary analysis will leverage non-targeted (differential features analysis) workflows of the entire LC-MS/GC-MS datasets through a combination of the vendor, open source, and commercial software tools, followed by a metabolite identification pipeline to identify statistically important features.

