### Sample Size

According to preliminary data from our pilot study, acupuncture was associated with a 9.6-mmHg (δ) greater reduction of 24-h average systolic blood pressure and a 7.7-mmHg greater reduction of 24-h average diastolic blood pressure as compared with sham acupuncture. Conservatively, we hypothesized that acupuncture is associated with a 7.5 mmHg reduction (σ) in 24-h systolic blood pressure compared to sham acupuncture. The significance level was set at 0.05 (α = 0.05, *Z*_α_ = 1.96), and the power of the test was set at 0.9 (1-β = 0.9, *Z*_1−β_ = 1.28). A total of 64 participants will be required in this study (32 in each group), including compensation for an anticipated dropout rate of 20%. Additionally, 10 healthy participants will be recruited as the healthy control group.

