### Statistical Analysis Plan

Clinical data will be analyzed with SPSS 24.0 software (SPSS Inc, Chicago, IL, USA). Continuous variables will be presented as mean and SD or as median and interquartile if they are not normally distributed. The baseline variables will be analyzed by the independent-samples t-test and Mann–Whitney U test, where appropriate. Categorical data will be presented as percentages. We will use the mixed-effects model to compare the effect of acupuncture vs. sham acupuncture on blood pressure from baseline to 4 and 8 weeks. The fixed effects are treatment arm, time, group^*^time interaction, and baseline outcome. For metabolomics data, the multivariate and univariate analysis will be performed in combination to determine the plasma metabolites that distinguish EH patients from a healthy subjects, and metabolites that exhibit significant changes before and after treatment in each treatment arm. We will use the Partial least square discriminant analysis (PLS-DA) in SIMCA-P (version 14.0; Umetrics, Umeå, Sweden) and the MetaboAnalyst (http://www.metaboanalyst.ca/MetaboAnalyst/) to fulfill the identification of differential metabolites between groups. All statistical tests will be two-sided, and statistical significance will be set at 5%.

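### One 5% level for every test, with no multiplicity control, also governs the untargeted metabolomic screen, where it would declare about 5% of the truly null features in each comparison

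*Protocol article*

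**What the plan says.** The protocol article, under Metabolomics Analysis, plans two steps. The first is a targeted look at Krebs-cycle metabolites and others from the group's previous studies. The second is untargeted: "Secondary analysis will leverage non-targeted (differential features analysis) workflows of the entire LC-MS/GC-MS datasets", "followed by a metabolite identification pipeline to identify statistically important features". No number of features is given.

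Under Statistical Analysis Plan, the article says: "For metabolomics data, the multivariate and univariate analysis will be performed in combination". The purposes are "to determine the plasma metabolites that distinguish EH patients from a healthy subjects" and to find "metabolites that exhibit significant changes before and after treatment in each treatment arm". That makes at least three comparisons. The multivariate tool is also named: "We will use the Partial least square discriminant analysis (PLS-DA) in SIMCA-P", together with MetaboAnalyst. The section then ends: "All statistical tests will be two-sided, and statistical significance will be set at 5" per cent.

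The Sample Size section uses the same level for the blood-pressure outcome, with a normal quantile of 1.96. No section mentions a false discovery rate, q-values, a Bonferroni threshold or permutation, and none sets the metabolomics tests apart from the 5% rule.

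**The concern.** A 5% two-sided level suits a single prespecified clinical comparison. Applied feature by feature to an untargeted dataset, it controls the error rate of each test but not the make-up of the resulting list. The list grows by one chance finding for every 20 null features tested, and features that pass go forward to identification.

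This matters because of what the article plans to do with the list. The metabolic profile is the fourth study aim in the Introduction. The Abstract expects insight into mechanism and says the results will inform a larger trial. The Discussions section hopes for metabolic signatures that predict response. A list with a substantial share of chance features is a weak basis for any of these.

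**Working it through.** **Inputs from the article.** Two-sided level 0.05 for all tests (Statistical Analysis Plan); quantile 1.96 (Sample Size); 64 patients, 32 per arm, and 10 healthy subjects (Sample Size); three named comparisons (Statistical Analysis Plan).

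**Assumed inputs.** The number of features m, the share that are truly null π0, and the power for features that truly differ. The article gives none of these, so ranges are shown.

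**Step 1: the stated level.** 2 × (1 − Φ(1.96)) = 0.0500. The article's 1.96 is the ordinary two-sided 5% level for one test.

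**Step 2: expected false declarations per comparison** = m × π0 × 0.05.

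| Features m | all null | 90% null | 80% null | 50% null |
|---|---|---|---|---|
| 100 | 5 | 4.5 | 4 | 2.5 |
| 500 | 25 | 22.5 | 20 | 12.5 |
| 1,000 | 50 | 45 | 40 | 25 |
| 5,000 | 250 | 225 | 200 | 125 |

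Correlation between features changes the spread of these counts, not their expectation. With 100 independent null features, the chance of at least one false declaration is 1 − 0.95^100 = 0.994.

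**Step 3: over the three named comparisons.** With 1,000 features, 3 × 50 = 150 if all are null, or 3 × 45 = 135 if 90% are null. Urine is also collected (Trial process chart; Sample Collection and Preservation), but the statistical section names only plasma for the comparison with healthy subjects. The total is therefore not doubled here.

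**Step 4: approximate share of declared features that are false** = 0.05π0 / [0.05π0 + power × (1 − π0)].

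| Null share π0 | power 50% | power 80% |
|---|---|---|
| 95% | 0.0475/0.0725 = 66% | 0.0475/0.0875 = 54% |
| 90% | 0.045/0.095 = 47% | 0.045/0.125 = 36% |
| 80% | 0.04/0.14 = 29% | 0.04/0.20 = 20% |
| 50% | 0.025/0.275 = 9% | 0.025/0.425 = 6% |

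**Step 5: simulation at the planned sizes** (400 runs, 1,000 independent null features). The unadjusted 5% rule declared a mean of 50.1 features for 64 against 10 (two-sample t-test) and 49.5 for 32 pairs (paired test). Benjamini-Hochberg at 5% declared a mean of 0.09 and 0.06. In the 64 against 10 case, also requiring a PLS-DA variable importance above 1 removed none of the 50.1. That filter is not in the article; it was tried only to see whether combining the two approaches would protect the list.

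**The case against.** The strongest reply is that this is an omission in a condensed article. A 5% level could be applied to adjusted p-values or q-values, the remedy below itself keeps 5%, and a fuller analysis plan could supply the method. But the article does more than stay silent. It fixes a level for all tests, directly after describing the metabolomics, and does not separate feature tests from clinical ones. The same level is tied to 1.96 in the sample size, which is an unadjusted single-test value. Nothing in the text supports reading it as an adjusted level for the features, so the sentence would need changing even if a fuller plan had an FDR rule.

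The reply is right about size, and three stronger readings should be resisted.

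- A reader might infer that 50 false metabolites per 1,000 features are to be expected outright. That holds only if every feature is null, the count of 1,000 is assumed, and an identification step stands between a feature and a metabolite.
- A reader might infer that the mechanistic conclusions would rest largely on false positives. At 90% null and 50% to 80% power, false features are a minority. A majority needs sparser effects, such as 95% null, and the article gives no basis for assuming that. It also puts the preset panel first and calls the untargeted work secondary.
- A reader might infer that the plan accepts an overfitted PLS-DA separation. On pure noise (26 against 26, 1,000 features), a two-component model reached 100% fitted accuracy but about 45% in 7-fold cross-validation. Yet the article nowhere says that fitted separation will be accepted without validation, and that simulation does not model the contrasts it specifies.

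It also stands that no efficacy or safety conclusion depends on this point.

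**Conclusion.** The concern holds as a badly fixed rule for the untargeted screen. Under the text as written, about 5% of truly null features would be declared in each of at least three comparisons. The result rests on the literal scope of the closing sentence and on assumed values for feature count, null share and power. Those assumptions change the size of the problem, not its direction: if many features truly differ, the false share is small (6% to 9% at half null); if few do, it is large. The metabolomic findings are affected and the primary 24-hour blood-pressure analysis is not. The rule should be changed before the feature data are analysed.

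**What to change.** Amend the closing sentence of the Statistical Analysis Plan section so that the unadjusted two-sided 5% level applies to the clinical tests only. Then state that:

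- untargeted features are declared by Benjamini-Hochberg FDR at 5%, separately within each biofluid and each comparison;
- the preset panel of Krebs-cycle and previously identified metabolites forms its own FDR family, so that it is not penalised for the size of the untargeted screen.

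FDR control suits a screen better than a Bonferroni threshold, which would be 0.05/1,000 = 0.00005 for 1,000 features. As a sensible addition, but not the core of this point, any claimed PLS-DA separation could be checked by comparing its cross-validated performance with a label-permutation distribution.

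The change is a few lines of wording and routine software output, with no new patients, samples or assays. The cost is that fewer features will be declared, including some that truly differ.

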## Discussions

Acupuncture reduces stress and is widely used as a non-pharmacological treatment for cardiovascular diseases and metabolic disorders (20, 47). However, the modulating effects of acupuncture on the cardiovascular and metabolic systems are not well understood so far. Here, we present the design and methodology of our ongoing randomized clinical trial which evaluates the efficacy and safety of acupuncture vs. sham acupuncture on blood pressure and metabolic profile among patients with EH. We will enroll 64 eligible patients and measure their blood pressure with the 24-h ABPM test after administrating 10 acupuncture sessions over 4 weeks. Meanwhile, we will determine the changes in the metabolic profile associated with the treatment effect, via targeted and untargeted metabolic profiling. Additionally, we will identify potential clinical variables and metabolic signatures that are predictive of treatment response to acupuncture among patients with EH. The study findings may have important clinical and research implications.

Till now, the role of acupuncture in blood pressure management remains unclear. Our previous systematic review of randomized clinical trials found inconsistent results concerning the effect of true vs. sham acupuncture on blood pressure, due to the risk of bias associated with sample size, control arms, and treatment population (16, 20, 48). Further, our understanding of the biological foundation of acupuncture is limited, especially in terms of cardiovascular and metabolic modulation. Although metabolic dysregulation has been closely linked to the pathogenesis of EH (49–51), fewer studies have been conducted to assess the metabolic changes in the non-pharmacological blood pressure treatment (23). Our study incorporates metabolomics technology in the design of a rigorous randomized control trial to characterize the metabolic signatures associated with changes in clinical outcomes. This study will provide preliminary data to support the design of a sufficiently powered, randomized controlled trial in the future, which will provide important clinical data to inform the non-pharmacologic management of EH, and physiological information to understand the biological underpinnings of acupuncture for blood pressure and metabolism regulations.

In addition to blood pressure and metabolic profile, this study measures the co-occurring sleep and cognitive symptoms, and health-related quality of life in EH patients, which is seldom addressed by previous studies. Insomnia and sleep disturbances are common and bothersome among EH patients (52). On the other hand, sleep disturbances also contribute to the onset of hypertension and disrupt blood pressure control, resulting in major cardiovascular events like stroke (53, 54). Further, hypertension leads to maladaptation of the cerebral circulation, resulting in dysregulation of cerebral blood flow, microvascular rarefaction, blood-brain barrier disruption, oxidative stress, and impaired neurovascular coupling, while these pathological alterations in cerebral microvessels would damage microvascular structure, network architecture and function, and contribute to the genesis of cerebral microhemorrhages, lacunar infarcts and white matter injury, causing and exacerbating cognitive impairment (55, 56). At present, those symptoms are inadequately monitored and poorly managed in research and clinical practice, leading to decreased quality of life, especially among older adults (57, 58). Our study will shed light on the effect of acupuncture on sleep and cognitive health among EH patients.

This study will also contribute to the identification of potential biomarkers predicting a more pronounced response to acupuncture among EH patients. The pathogenic process of EH is multifactorial; precision treatment targeting a specific signaling pathway or a certain subtype of the population is developed in the conventional treatment paradigm. However, it remains unexplored in non-pharmacologic treatment. Our pilot study showed that specific metabolic pathways are involved in the regulation of blood pressure by acupuncture, which is promising in outcome prediction during the acupuncture treatment (24, 25). Leveraging metabolomics approaches, we will be able to capture metabolic signatures associated with treatment response to acupuncture. Previous studies also linked patient psychosocial characteristics [such as patient expectancy (59)] and patient characteristics [such as Chinese medicine-based body constitution categorization (60)], to the variations in response to acupuncture treatment for high blood pressure. We will further explore potential phenotypic biomarkers that may predict treatment response to acupuncture, which may provide evidence to inform precision non-pharmacologic blood pressure management.

## Ethics Statement

The studies involving human participants were reviewed and approved by the Sichuan Regional Ethics Review Committee on Traditional Chinese Medicine, which belongs to the Regional Ethical Review Committee of Traditional Chinese Medicine in Sichuan province (reference number: 2021KL-006). Written informed consent will be obtained from all participants.

## Appendix

**Table 1 TA1:** Detailed location of acupoints.

**Acupoints**	**Location**
Quchi (LI-11)	Flexing the elbow, on the lateral end of the transverse cubital crease, at the midpoint between Chize (Lu-5) with the lateral epicondyle of humerus.
Neiguan (PC-6)	On the palmar side of the forearm, on the line connecting Quze (PC-3) with Daling (PC-7), 2 cun above the transverse crease of wrist, between the tendons of palmaris longus and flexor carpi radiadis.
Zusanli (ST-36)	On the anterior side of the shank, 3 cun below Dubi (ST-35), one horizontally placed figure distance lateral to the anterior border of the tibia.
Taichong (LR-3)	On the dorsum of the foot, in the depression proximal to the first metatarsal space.
